### Blinding

It is noteworthy that the nature of this study does not allow for blinding the researcher and participants. To blind data collectors, the questionnaires for the postpartum stage will be completed by the researcher's assistant. Also, the data analyst will be blinded to group assignments.

### Intervention

After assigning the participants to the study groups, socio-demographic and obstetrics characteristics questionnaires will be filled out for all of them. Then the researcher will implement the WHO intrapartum care model for those in the intervention group, whereas those in the control group will receive routine care by staff. The implementation of the study is in the form of multidisciplinary teamwork. The researcher who will implement the intrapartum care model is PhD student of midwifery (first author). She has attended workshops on making childbirth pleasant and physiologic childbirth and also worked for four years as a physiologic childbirth tutor in a health center. In the case where advice is needed or in unpredictable high-risk cases, the gynecologist involved in the study project will be contacted (second & fourth authors). The implementation of care will be monitored by the project supervisors who are reproductive health specialists (third and corresponding authors).

The intervention based on the 9 components of the WHO intrapartum care model is as follows:
1.Respectful labor and childbirth care: To implement this component, a respectful care scale will be used. Four sub-domains of this scale included: friendly care, abuse-free care, timely care, and discrimination-free care. Calling the mother by her first name, talking to her in a familiar language, respecting her beliefs and values, not delaying the provision of care, and behaving without discrimination are the features of respectful care (28).2.Emotional support from a companion of choice: A companion selected by the participant (in the intervention group) will be present during the labor in coordination with Metron and the supervisor. A previous study proposed that the participant's companion should take the following responsibilities: Support the woman (stay with her, calm her down, massage her, show her affection, and encourage and stimulate her), behave correctly when the woman faces fatigue, anxiety and worry, cries or screams or feels helpless, observe the regulations (wear standard clothes, avoid eating, smoking, or touching the equipment and devices), and inform the staff whenever it is necessary to leave the hospital). The companion can request information from the staff. It has been also emphasized that the companion must respect the privacy of other women (29). In this study, all these items will be recommended to the selected companion of the pregnant woman, and the researcher will monitor their observance by the companion. In cases where no one can accompany the participant, the researcher will play this role for her if she agrees. Considering that the companion's role will be to provide supportive care to the woman (as mentioned above), it seems that performing this role does not conflict with the tasks of the researcher in labor.3.Effective communication by staff: Effective communication by staff: characteristics of effective communication according to WHO include the following: (a) informing women and their families about the advantages and disadvantages of methods and use/non-use of technologies during maternity care; (b) listening respectfully to women and their families; (c) participation women and their families in decision-making and respecting their preferences (13).4.Pain relief strategies: The researcher in this study will employ non-pharmacological pain relief techniques, such as teaching diaphragmatic breathing with proper inhalation and exhalation, thermotherapy, position change, and massage (30) if the participant agrees. If necessary, pharmacological pain relief methods will be used at the discretion and under the supervision of a gynecologist involved in the project.5.Regular monitoring of labor, documentation, auditing, and feedback: Both the maternity ward staff and the researcher will document the labor and childbirth events. In addition, the researcher will closely and regularly monitor obstetric care during labor, childbirth, and in the first two hours after delivery and then provide necessary feedback. Regular monitoring of labor includes measures such as intermittent control of the fetal heart rate using a fetal doppler, injection of uterotonic agents (oxytocin or misoprostol), and controlled umbilical cord traction to prevent postpartum hemorrhage, delayed umbilical cord ligation, and regular postpartum maternal monitoring for vaginal bleeding, uterine tonus, and vital signs (15). Labor documentation involves activities such as the use of partograms.6.Receiving oral fluids and food: The participants' companions in the intervention group will be provided with a recommended list of easily digested foods or liquids to prepare (e.g., drinking water, juices, dates, biscuits, and cakes). However, the participants will be free to consume whatever they desire in small amounts divided into several portions.7.Maternal mobility and selection of the position of choice: According to a previous study, sitting, walking, semi-sitting, four-legged, and lateral positions (both sides) will be considered for the participants in the intervention group during the first phase of labor (31). The researcher will train the participants in each of these positions and explain to them its advantages. The participants will be asked to begin with any position that is easier for them, hold each position for 10 min, and take a 10-min rest between two positions. They should also repeat these five positions at 5-cm, 7-cm, and 10-cm of cervical dilatation. Based on a previous study, the participants in the intervention group will be recommended to walk for an hour several times a day on average depending on their tolerance and duration of labor (32). Eventually, the amount of mobility and type of positioning will be at the mother's discretion8.A pre-decided referral plan: Since the research setting includes sub-specialty hospitals, there will be no need for referral for the participants to receive higher levels of care. Nevertheless, they will be regularly monitored during labor and in the early postpartum period to coordinate with the gynecologist as soon as possible if necessary and make prompt decisions. It should be noted that considering the great importance of regular examination of women during labor and delivery, this component of the WHO model will be performed in both control and intervention groups.9.Continuity of care: To observe the continuity of care in this study, the researcher will provide the participants of the intervention group with antepartum, intrapartum, and postpartum care one day after childbirth in the maternity ward, on the tenth day, and the fortieth day after delivery.

### Routine care

Routine care in the study settings often includes medical procedures ordered by residents of gynecology. Midwives often take care of several women and opportunities for providing midwifery-led care are very limited. Despite a clear definition of the components of respectful care, not all women receive this model of care, and other components of the intrapartum care model are not prioritized as much as medical and clinical care.

The obstetric information of the participants (e.g., duration of the active phase of labor, duration of the second and third phases of labor, Apgar score, etc.) will be also recorded during and immediately after labor. Moreover, Wijma's delivery fear scale (DFS) will be filled out for the participants before the active phase of labor and then at 7–8 cm of cervical dilation. The participants of both groups will be followed up for 6 weeks after labor and then they will be invited to a relatively quiet place to complete the Childbirth Experience Questionnaire (CEQ 2.0), the Edinburgh Postpartum Depression Scale (EPDS), the Post-Traumatic Stress Disorder (PTSD) Symptom Scale (PSS-I), the Pregnancy and Childbirth Questionnaire (PCQ), and a checklist on willingness to give birth to another child. If answering all the postpartum questions is out of the mother's patience, the interview will be conducted on two separate dates determined by the mother.

### Outcomes

Primary outcomes included birth experience, fear of childbirth, and mother's satisfaction with the quality of intrapartum care.

Secondary outcomes included postpartum depression, post-traumatic stress disorder, desire for giving birth to another child, normal vaginal childbirth, Apgar score, exclusive breastfeeding, duration of the first stage of labor, duration of the second stage of labor, duration of the third stage of labor, and face, content, and construct validity and also the reliability of the Pregnancy and Childbirth Questionnaire (PCQ).

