#### Specific objectives

1.To compare the childbirth experience between the intervention (receiving intrapartum care based on the WHO model) and control group (receiving routine hospital care)2.To compare the fear of childbirth between the study groups3.To compare the quality of intrapartum care between the study groups.

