### Sample size

The sample size was calculated in G-Power based on the two primary outcomes of the childbirth experience and fear of childbirth. According to the findings of Shakarami et al. (26) regarding the fear of childbirth and assuming *M*_1 _= 69.3, *M*_2 _= 58.9 (considering a 15% clinically significant increase caused by the intervention based on expertise panel), SD_1 _= SD_2 _= 8.5, two-sided *α* = 0.05, and test power = 95%, the calculated sample size (*n*) was 19. Moreover, according to the findings of Ghanbari et al. (27) about childbirth experience and assuming *M*_1 _= 2.71, *M*_2 _= 3.25 (considering a 20% clinically significant increase caused by the intervention based on expertise panel), SD_1_ = SD_2_ = 0.73, two-sided *α* = 0.05, and test power = 95%, the sample size (*n*) increased to 49. Finally, assuming an attrition rate of 10%, the final sample size (*n*) in each group will be 54. This sample size has the power of 99% to test between-group differences in terms of fear of childbirth.

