### Data analysis

The obtained data will be entered into the software using the double data entry approach and will be statistically analyzed in SPSS 24. The socio-demographic and obstetric information will be described using descriptive statistics, i.e., frequency, percentage, and mean (standard deviation) if the data follow a normal distribution pattern or median (the 25th to 75th percentile) if they do not follow a normal distribution pattern. The independent t-test and the chi-square test in the bivariate analysis and the general linear model (after controlling for the socio-demographic and obstetric characteristics) in the multivariate analysis will be also employed to compare the study groups in terms of the childbirth experience, fear of childbirth, postpartum depression, PTSD symptoms, duration of childbirth procedure, Apgar score (one and five minutes after birth), willingness to give birth to another child, and type of delivery. The missing data will be handled by the multiple imputation method). The sensitivity analysis will be done by comparing the results of the modified intention to treat analysis with the imputed data analysis.

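### Three primary outcomes are named, but the sample size section counts two and the list of group comparisons omits the third, so its power and the overall error rate are not fixed

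*Protocol article*

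**What the plan says.** The Outcomes section names three primary outcomes: "Primary outcomes included birth experience, fear of childbirth, and mother's satisfaction with the quality of intrapartum care". This is not a slip in one sentence. The Specific objectives, listed apart from the secondary objectives, cover the same three, the last being "To compare the quality of intrapartum care between the study groups".

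The Sample size section counts differently: "The sample size was calculated in G-Power based on the two primary outcomes of the childbirth experience and fear of childbirth". For fear of childbirth it gives "two-sided *α* = 0.05, and test power = 95%, the calculated sample size (*n*) was 19"; for childbirth experience, "two-sided *α* = 0.05, and test power = 95%, the sample size (*n*) increased to 49". It gives no effect, standard deviation or power for quality of care.

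The Data analysis section says that t-tests, chi-square tests and a general linear model will be used "to compare the study groups in terms of the childbirth experience, fear of childbirth, postpartum depression, PTSD symptoms, duration of childbirth procedure", and continues through Apgar score and willingness to have another child to type of delivery. Quality of care is not on the list. Exclusive breastfeeding, a named secondary outcome, is also absent. The seven intrapartum items of the PCQ are nevertheless to be collected (Routine care; Data collection tools).

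**The concern.** The set of primary outcomes decides what counts as a positive trial, and this document gives two different sets. Under the longer one, a primary outcome is collected but has neither a stated group comparison nor a stated power. The 0.05 used in each sample size calculation takes no account of there being several primary outcomes, and the article does not say whether one positive result is enough or all are needed.

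If this stays open, the choice could be made after the results are known. Neither the women nor the researcher delivering the care can be blinded, so the confirmatory claim needs a definition fixed in advance.

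**Working it through.** **Inputs from the Sample size section**
- Childbirth experience: means 2.71 and 3.25, SD 0.73, so d = 0.54/0.73 = 0.740.
- Fear: means 69.3 and 58.9, SD 8.5, so d = 10.4/8.5 = 1.224.
- Two-sided alpha 0.05, power 95%, 10% attrition, 54 per group. About 49 per group are evaluable (54 × 0.9 = 48.6).

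**1. The plan's own figures.** Two-sample t-test power from the noncentral t, with 2n − 2 degrees of freedom and noncentrality d√(n/2):
- Childbirth experience: 48 per group gives 94.8% and 49 gives 95.2%, so n = 49, as stated.
- Fear: 18 per group gives 94.6% and 19 gives 95.6%, so n = 19, as stated.
- Fear at 49 per group: above 99.9%, consistent with the stated 99%.

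Both stated powers are right for each outcome taken alone at 0.05.

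**2. If any one of three primaries at 0.05 counts as success.** With independent outcomes and no true effect on any, the familywise error is 1 − 0.95³ = 1 − 0.857 = 14.3%. Simulation with equal correlations between the outcomes gives about 13.6% at 0.3, 12.6% at 0.5 and 11% at 0.7. For the two sized outcomes only, it is 1 − 0.95² = 9.8% if independent. The correlations are assumptions; the document gives none.

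**3. If all three must succeed.** Alpha stays at 5%. Power is the joint probability, and the PCQ effect is not stated. Assuming independence and 49 per group, joint power = 0.952 × (more than 0.999) × PCQ power:

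| Assumed PCQ effect (SD) | PCQ power | Power for all three |
|---|---|---|
| 0.5 | 68.8% | 65.5% |
| 0.6 | 83.6% | 79.6% |
| 0.74 | 95.2% | 90.6% |

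**4. Childbirth-experience power under a multiplicity rule, 49 per group**

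| Two-sided alpha | Power |
|---|---|
| 0.05 | 95.2% |
| 0.025 | 91.5% |
| 0.0167 | 88.7% |

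Fear stays above 99.9% at all three levels.

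Under Holm with three outcomes:
- If fear has its planned effect it is almost always rejected first. Childbirth experience then faces 0.025, or 0.05 if the PCQ is also rejected. Simulated power is about 92% with no PCQ effect and about 95% with a PCQ effect of 0.74 SD.
- The floor is 88.7%. A p-value at or below 0.0167 is always rejected by Holm, whatever the other two show. With no effect on fear or PCQ, simulated power is about 88.8%.

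**5. What 49 per group detects on the PCQ.** At alpha 0.05, a difference of 0.57 SD with 80% power and 0.74 SD with 95% power. At alpha 0.0167 these become 0.66 SD and 0.83 SD.

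**The case against.** The strongest reply is that the error-rate argument rests on a rule the document does not state. The Data analysis section gives no significance level, the 0.05 appears only in the sample size inputs, and nowhere is one positive outcome said to suffice. A multiplicity method is also something an article may leave to a statistical analysis plan. This stands. A reader might infer that the trial is designed to declare success on any one of three tests at 5%, with a 14.3% error rate. The text does not say so, and 14.3% is itself a ceiling that assumes independence. The childbirth experience questionnaire has a professional-support domain that overlaps in content with the PCQ, so positive correlation is likely.

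A reader might also infer that the stated powers are wrong, or that quality of care was deliberately dropped. Neither is supported. The 95% and 99% reproduce, and the Sample size section never claims power for a joint question. The comparison list also omits exclusive breastfeeding, so it looks incomplete rather than selective. The planned t-test and linear model could be applied to the PCQ score directly. Nor is it an error in itself to size on fewer outcomes than are named, and the protocol says the PCQ has not been validated in Iran, so a local SD may not have been available.

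What the reply does not remove is the contradiction. An analysis plan can add a testing rule, but it cannot make one section's two primary outcomes agree with another's three. Any alpha-splitting rule it added would also change the level at which the 95% was calculated.

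**Conclusion.** The point holds as an internal inconsistency with consequences that depend on the success rule. Three primary outcomes are named, two are sized, and the third is missing from the listed comparisons. With any-one success at 0.05 the familywise error is up to 14.3%, and about 11% to 12.6% at assumed correlations of 0.7 to 0.5. With all three required, alpha holds but power is not established: roughly 65% to 91% for assumed PCQ effects of 0.5 to 0.74 SD under independence. Neither rule gives both 5% error and an established 95% power for three primaries. The 95% for childbirth experience is valid for that outcome alone at an unadjusted 0.05. The loss from correcting this is modest, and the trial's size is not in question.

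**What to change.** Make the Specific objectives, Sample size, Outcomes and Data analysis sections name the same primary outcomes. Add the 7-item PCQ score to the between-group comparisons, and exclusive breastfeeding as well while the list is being edited. Then choose one of the following.

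- **(a) Keep three primaries.** Test them with Holm at an overall two-sided 0.05. Restate childbirth-experience power at 49 per group as about 92% if fear has its planned effect, and 88.7% at worst. State that 49 per group detects a PCQ difference of about 0.57 SD with 80% power and 0.74 SD with 95% power at alpha 0.05, and larger differences at an adjusted level.
- **(b) Name one primary.** Childbirth experience drives the sample size, so making it the single primary keeps 95% power at 0.05. The price is that fear of childbirth and quality of care, both specific objectives now, become key secondary outcomes.

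Either option changes wording only; 108 women remain enough. Under (a) the stated power for childbirth experience falls by about 3 points if fear behaves as planned, and by 6.5 points at worst (95.2 − 88.7). The choice should be fixed before outcome data are seen by group.

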### Data collection tools

A socio-demographic characteristics questionnaire: This questionnaire will consist of questions about the participant's age, spouse's age, age at marriage, educational attainment, job status, religion, ethnicity, marital status, housing status, household income, place of residence (rural or urban areas), weight before pregnancy, smoking, alcohol, and drug abuse before and during pregnancy.

Obstetrics history questionnaire: This questionnaire contains questions about gestational age, number of pregnancies, number of abortions, attendance at pregnancy classes, pregnancy status (wanted or unwanted), type of previous delivery (if there have been previous pregnancies), and history of pregnancy complications.

Childbirth Experience Questionnaire (CEQ2.0): This 25-item questionnaire measures four main domains of women's childbirth experience: own capacity (sense of control, personal feeling about childbirth, and labor pain), professional support (obstetric information and care), perceived safety (a sense of security and childbirth memories), and participation (a woman's ability to control her postures and movements and relieve pain during labor and delivery). Twenty-two of the 25 items in this questionnaire are scored using a 4-point Likert Scale (1: I agree, 2: I often agree, 3: I often disagree, and 4: I disagree) and the remaining 3 items are scored based on a Visual Analogue Scale (VAS) (1, 2, 3, or 4 points are given to scores 0–40, 41–60, 61–80, and 81–100, respectively). The validity and reliability of the CEQ 2.0 have been proven in a population of American women. The items with negative concepts (experiencing severe pain, fatigue, fear, and having a bad memory) receive negative scores. Higher mean scores on this questionnaire indicate a more positive childbirth experience (33).

Delivery Fear Scale (DFS): This scale was developed by Wijma to measure women's fear of childbirth during labor (34). It is a valid self-assessment questionnaire that measures fear of childbirth during labor through scores ranging from 1 (totally disagree) to 10 (totally agree). Higher scores indicate higher levels of childbirth fear (35).

Post-Traumatic Stress Disorder (PTSD) Symptom Scale (PSS-I): This scale consists of 17 items that are scored using a Likert scale. The subscales of PSS-I are re-experienced symptoms (4 items), avoidance symptoms (7 items), and symptoms of motivational reactions (6 items). If the respondent exhibits one or more re-experiencing symptoms, three or more avoidance symptoms, and two more symptoms of motivational reactions, he/she is diagnosed with PTSD. The total score on this scale ranges between 0 and 51 (36).

Edinburgh's Postpartum Depression Scale: This scale was developed by Cox et al. for measuring prenatal and postpartum depression in women. It consists of 10 four-choice questions, some of which are scored from low to high levels of depression (items 1, 2, and 4) and others are scored from high to low levels of depression (items 3, 5, 6, 7, 8, 9, and 10) with a score ranging from 0 to 3 is given to each choice, and the minimum and maximum total scores on this scale are 0 and 30, respectively. The validity of this scale was assessed by calculating the coefficient of correlation between this scale and Beck's Depression Inventory; the correlation coefficient for these tools was obtained at 0.78. In addition, the reliability of this scale was tested by calculating Cronbach's alpha and using split-half reliability; the results showed that the estimated overall reliability of this scale was 0.75 (37).

The checklist on willingness to give birth to another child: This checklist includes one Yes/No question about the women's willingness to give birth to another child.

Pregnancy and Childbirth Questionnaire (PCQ): This 25-item questionnaire was developed by Truijens et al. to measure the postpartum views of mothers about the quality of pregnancy and childbirth care. Of the 25 items of PCQ, 18 items measure experiences and perceptions of pregnant women about the quality of prenatal care in two domains: personal behavior (11 items; Cronbach's alpha = 0.87) and educational information (7 items; Cronbach's alpha = 0.90). The remaining 7 items measure puerperal women's experiences with the quality of intrapartum care (Cronbach's alpha = 0.88) and just these items will be used in this study (38). The items of this questionnaire are formulated in positive and negative propositions and scored using a 5-point Likert scale, from 1: totally agree to 5: totally disagree. The total score on PCQ ranges between 25 and 125, and higher scores indicate higher levels of satisfaction (35). The 7 items of this questionnaire that measure puerperal women's experiences of the quality of intrapartum care will be used in this study.

Implementation success rate checklist: This checklist will be designed to determine the success rate of implementation of each intervention component for each woman. This rate will be calculated by determining the answer yes in case of implementation or no in cases of non-implementation due to mothers' unwillingness or other reasons.

Partogram: A Partogram is a simple but valid chart used to monitor labor and prevent prolonged and obstructed labor focusing on observations related to maternal and fetal conditions as well as the labor progress. It provides the healthcare personnel with a pictorial overview of the labor. The information recorded on the Partogram includes maternal health, fetal health, childbirth process, and childbirth management. Partograms form an early warning system that greatly helps decision-making on the timely referral of pregnant women (39). Length of labor stages, spontaneous vaginal childbirth, the use of oxytocin, analgesia, amniotomy or episiotomy, degree of perineal tears, and also the Apgar score will be obtained from this form.

All questionnaires will be completed through interviews in a quiet place. Due to the large number of questionnaires, implementation of those will be tested prior to the study. If the interview is long and the mother is tired, two sessions will be considered.

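### The printed scoring key for the CEQ 2.0, a primary outcome and the one that sets the sample size, makes the best childbirth experience score lowest, against the stated meaning of a high score

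*Protocol article*

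**What the plan says.** The Outcomes section reads: "Primary outcomes included birth experience, fear of childbirth, and mother's satisfaction with the quality of intrapartum care". The first of these is measured with the CEQ 2.0 and the third with the PCQ.

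For the CEQ 2.0, Data collection tools states:
- "Twenty-two of the 25 items in this questionnaire are scored using a 4-point Likert Scale", with the codes "1: I agree, 2: I often agree, 3: I often disagree, and 4: I disagree".
- The other three items are visual analogue scales: "1, 2, 3, or 4 points are given to scores 0–40, 41–60, 61–80, and 81–100, respectively". Neither the anchors nor the content of these items is given.
- Only one group of items is singled out: "The items with negative concepts (experiencing severe pain, fatigue, fear, and having a bad memory) receive negative scores".
- The total is then interpreted as follows: "Higher mean scores on this questionnaire indicate a more positive childbirth experience".

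The Sample size section plans on a CEQ mean of 2.71 rising to 3.25 and calls this a 20% increase due to the intervention.

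For the PCQ, the same tools section describes 25 positively and negatively worded items, coded from 1 (full agreement) to 5 (full disagreement). It mentions no reversal. It adds: "The total score on PCQ ranges between 25 and 125, and higher scores indicate higher levels of satisfaction". Of the 7 intrapartum items it says that "just these items will be used in this study", and it repeats that restriction at the end of the paragraph.

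**The concern.** On the CEQ 2.0, a woman who agrees with a positive statement about her birth gets 1 point, and a woman who disagrees gets 4. The only items marked for different treatment are the negative ones. Once those are turned round, they also give 1 for the good answer. The whole Likert part then runs from good (low) to bad (high), while the text says that high is good.

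The CEQ 2.0 is a primary outcome, and its 49 per group, raised to 54 for attrition, is what sets the trial's size. If the syntax follows the printed key and the report follows the printed interpretation, a beneficial intervention would be reported as harmful, or the reverse. The analyst is to be blinded to group, so the group labels would not reveal the inversion.

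The PCQ paragraph raises a lesser question of the same kind: which way its 7 items point, and what range their total has.

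**Working it through.** **1. The plan's own figures.** From Sample size: 2.71 × 1.20 = 3.252, so the planned change is a rise of 0.54. With SD 0.73, two-sided α = 0.05 and power 95%, a t-based calculation gives 48.5, hence 49 per group, as stated. The fear outcome (69.3 against 58.9, SD 8.5) gives 18.4, hence 19, as stated. The planning therefore treats a higher CEQ mean as better.

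**2. CEQ Likert items under the printed key.** Read the sentence on negative items as reverse scoring, so that their score is 5 − raw.
- Best experience: positive items agreed with = 1; negative items disagreed with = 5 − 4 = 1. Mean over the 22 items = 1.
- Worst experience: positive items disagreed with = 4; negative items agreed with = 5 − 1 = 4. Mean over the 22 items = 4.

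**3. All 25 items.** The anchors of the three visual analogue items are not given, so both directions are tried.

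| Visual analogue items | Best experience | Worst experience |
|---|---|---|
| High value is good | (22×1 + 3×4)/25 = 34/25 = 1.36 | (22×4 + 3×1)/25 = 91/25 = 3.64 |
| High value is bad | (22×1 + 3×1)/25 = 25/25 = 1.00 | (22×4 + 3×4)/25 = 100/25 = 4.00 |

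In both rows a high mean is a worse experience. Three items cannot overturn 22.

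**4. If no item were reversed.** The direction would then depend on how many of the 22 items are positive, which the article does not say. As an illustration, 18 positive and 4 negative items give a best Likert mean of (18×1 + 4×4)/22 = 1.55 and a worst of (18×4 + 4×1)/22 = 3.45, still inverted. At 11 and 11 both equal 2.5 and the score says nothing. Non-reversal restores the stated direction only if negative items are the majority.

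**5. Effect on the inference.** If every item is flipped, the score becomes 5 − x. The planned means 2.71 and 3.25 become 2.29 and 1.75. The absolute difference is still 0.54 and the SD is still 0.73. The sample size, power and two-sided p-value are the same; only the sign changes.

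**6. PCQ range.** 25 items × 1 to 5 gives 25 to 125, the printed range. The 7 items used give 7×1 = 7 to 7×5 = 35. A total above 35 cannot occur in this trial.

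**7. PCQ direction.** If the negative items are reversed (6 − raw), the most satisfied woman scores 7 and the least satisfied 35. If the positive items are reversed instead, it is 35 and 7. If nothing is reversed, the result depends on the unstated split: 4 positive and 3 negative gives best 4×1 + 3×5 = 19 and worst 4×5 + 3×1 = 23; 3 and 4 gives best 23 and worst 19. The text does not settle which applies.

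**The case against.** The strongest reply is that the intended direction of the CEQ 2.0 is clear. The tools section says high is good, and the sample size treats a rise as benefit. The response labels were then probably printed the wrong way round for an instrument whose evaluation is cited, and a uniform flip leaves the test unchanged. This stands as to intent and as to power. It does not remove the contradiction: the codes are the part of the text from which scoring syntax is written, and they give the opposite score. Nor is this only the condensation usual in an article. The codes are stated, and for the depression scale the same section lists by number which items run each way.

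Three stronger readings are tempting, and the article does not support them.
- A reader might infer that the three visual analogue items run against the other 22, so that the CEQ mean mixes directions and dilutes the effect. Without the anchors this cannot be known.
- A reader might infer that the PCQ is also scored backwards. The codes conflict with the stated meaning for positive items but fit it for unreversed negative ones. With neither the split nor the reversal stated, no direction follows. An item-level reversal list is also something an article may leave to the full protocol.
- A reader might call the range of 25 to 125 wrong. It is right for the full form, and no calculation in the article uses it. It simply does not apply to the 7-item score.

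**Conclusion.** The CEQ 2.0 contradiction holds. Under the printed key the best possible mean is 1.00 to 1.36 and the worst 3.64 to 4.00, so the planned move from 2.71 to 3.25 would be a deterioration. This assumes that the sentence on negative items means reverse scoring. If it were meant to turn the positive items round instead, the conflict would vanish, but the text does not say so. What is at risk is the direction of the conclusion on a primary outcome. The sample size and power are not affected by a uniform flip, and a loss of power through mixed directions is not shown.

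For the PCQ, only a clarification is needed. The analysed total runs from 7 to 35, and its alignment with satisfaction is not stated.

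**What to change.** For the CEQ 2.0, state that positive items score from agree = 4 to disagree = 1, that negative items are reversed, and that the three visual analogue items (with their anchors given) are aligned the same way before the 25 items are averaged. Confirm that the 2.71 in the Sample size section comes from a score built with this key. If it does not, put it on this key and check the assumed gain again.

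For the PCQ, state that the 7 intrapartum items are aligned so that a higher score means more satisfaction, name those that are reversed, and give the range of the analysed total as 7 to 35.

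The cost is a few sentences of protocol text and the matching scoring syntax, settled before the data are analysed. Questionnaires and data collection stay as they are.
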